#### Ad b) Antidepressant algorithm

An earlier study in the USA reported that only 46% of outpatients with care management who were treated with antidepressants at their local academic medical centre received adequate antidepressant treatment, thus reflecting a minimum standard of treatment [58]. There are further indications that chronically ill patients may require individually tailored antidepressant treatment [59]. Therefore, to enhance efficiency and adherence to the medication, a step-up antidepressant algorithm will be tailored to patients with DM, CVD, and COPD, consisting of two different types of antidepressant medication, i.e. selective serotonin reuptake inhibitors (SSRIs) and tricyclic antidepressants (TCAs).

Two antidepressants will be tested in two periods of nine weeks. If, after 18 weeks there is no improvement, the patient will be offered different kinds of treatment. In the choice of antidepressants, interactions with medication for chronic illnesses and potential palliative side-effects have been taken into consideration. If a patient is already taking antidepressants, but is still suffering from depression, the treatment is considered to be unsatisfactory, and after the required wash-out period of several weeks, the algorithm will commence. The PHQ-9 will be used to screen for and monitor the course of depression. The feasibility of the PHQ-9 to evaluate and guide a step-up algorithm has already been proven in outpatients in the primary care setting [40,60] Therefore, in the present study, the PHQ-9 will be used in the same way. The care managers will discuss the effects of the medication and the potential side-effects with the patient, and report to the psychiatrist. The psychiatrist will follow this process closely to determine whether the treatment is satisfactory.

Earlier studies have shown that the prescription of antidepressants for patients suffering from DM type I and II is safe and effective. Certain SSRIs, such as duloxetine, may also even be effective in the treatment of painful diabetic neuropathy [61,62]. However, knowledge about the interaction and side-effects of antidepressants in chronically ill patients has not yet been structured into a protocol tailored to the needs of patients with DM, CVD, and COPD.

#### Ad c) Problem Solving Treatment (PST)

Hawton and Kirkhave developed a brief psychological intervention based on the Problem Solving Therapy by D'Zurilla et al. [63] that uses the behavioural perspective, but is less time-consuming [64]. PST will be administered by nurses in 6–12 sessions, depending on the progress according to the PHQ-9 scale. The problem-solving approach consists of seven stages, and is based on the assumption that emotional problems are often induced by problems in everyday life.

Problem Solving Treatment has been found to be effective for treating MDD when provided by trained community nurses [65]. It is further significantly more effective than placebo treatment, and also more effective than antidepressant medication alone for patients in primary care [66].

The first session of PST will last for one hour, in which a clear focus of the treatment is established, based on the patient's current problems. Follow-up sessions will last for thirty minutes.

#### Ad d) Manual-guided self-help

The patient will receive a standardised treatment manual, specifically tailored to coping with depression and chronic illness, and will work through this manual. It consists of various chapters, focusing on relaxation, sleeping, exercise and cognitions, and it also gives dietary suggestions. The progress made by the patient is discussed every week or every other week between the patient and the care manager. Willemse et al. found that this kind of intervention is more effective than CAU, at least for patients in primary care with a sub-clinical depression [67]. Relaxation therapy on its own has been found to be useful as a complementary approach to depression [29].

Patients suffering from depression often experience difficulties in the sleep-wake-rhythm. The presence of these difficulties is also one of the criteria in the classification of MDD [68]. DM patients with painful peripheral neuropathy were also found to suffer considerably from sleeping problems[69]. For patients with chronic illnesses, sleeping problems are significantly correlated with poorer mental health, diminished work productivity and work quality, and greater use of the health care services [70]. Hence, the treatment of sleeping problems will be an important focus of this intervention.

Furthermore, exercise to improve general physical condition will be stimulated. Tkachuk and Martinhave extensively reviewed studies focusing on exercise therapy for patients with psychiatric disorders, and found that exercise has a positive effect, among other things, on depression [71]. In chronically ill patients with comorbid depression, exercise training was found to reduce the severity of the depression and to have a positive influence on indicators of illness risk factors [72-74]

The dietary intervention will focus on a healthy diet, losing weight and on taking omega-3 fatty acids. McElroy et al. concluded in their review that an overlap exists between mood disorders and obesity [75]. Several studies also indicate an association between omega-3 fatty acids and depression. For example, Su et al. found that omega-3 fatty acids could improve the short-term course of illness, and were well tolerated in patients with MDD [76]. The supplementation of omega-3 fatty acids was also found to be helpful in treating depression in patients with DM type 2 and in treating patients with heart diseases [77,78]

### Treatment of the patients in the control group

Half of the included patients function as a control group, in which they will receive CAU. The actual content of the CAU treatment (e.g. medication and number of contacts with physicians) will be assessed with the 'Scale assessing contacts between patients and practitioners' ('Contacten met dokters en andere behandelaars') and the 'Scale assessing medical utilization of health services' ('Vragenlijst medische consumptie') [57].

### Data collection

Data will be collected by the Trimbos Institute in co-operation with the Onze Lieve Vrouwe Gasthuis. After giving informed consent, the patients will receive assessment questionnaires by mail at baseline (T_0_), 3 (T_1_), 6 (T_2_), 9 (T_3_), and 12 months (T_4_) after inclusion. The modified 'Tailored Design Method' [79] will be used in this study to recruit the patients.

### Outcome parameters

The use of questionnaires in the hospital setting has a long tradition. Several of the questionnaires used in this study have already been used for earlier studies of patients in the hospital setting (e.g. PHQ-9 [80], IDS-SR [81], SF-36 [82]) and proved feasible. Although physical symptoms such as fatigue could be misinterpreted as depressive symptoms, in outpatients with general physical disorders no other diagnostic criteria for the diagnosis of MDD are needed [83,84].

Baseline measurements will take place before inclusion (T_0_). The first follow-up measurement will take place at the end of the treatment, i.e. after 3 months (T_1_), and further follow-up measurements will take place after 6 (T_2_), 9 (T_3_) and 12 months (T_4_).

#### 1. Primary outcome measure

##### Severity of depressive symptoms

The severity of the depressive symptoms is the primary outcome, and will be measured according to the depression sub-scale of the PHQ (PHQ-9). The PHQ-9 is a brief instrument that scores each DSM-IV criterion of a major depressive disorder on a scale ranging from zero (not at all) to three (nearly every day) [47]. The PHQ-9 has been found to be a valid and reliable instrument to measure the severity of depression in patients with different medical backgrounds [47]. In an earlier study, the PHQ-9 was used successfully for the diagnosis of MDD in diabetic patients [85].

An improvement of more than five points on the PHQ-9 can be considered a clinically relevant difference [86]. The PHQ-9 will be administered at baseline and during treatment at least every other week (before each appointment with the care manager). After treatment, the PHQ-9 will be administered every three months (3 (T_1_), 6 (T_2_), 9 (T_3_) and 12 (T_4_) months after baseline).

#### 2. Secondary outcome measure

##### Cost-effectiveness

In addition to the improvement of severity of symptoms, the cost-utility of collaborative care compared to CAU is assessed in this study. Therefore, an estimation of the direct medical costs and the costs due to production losses (productivity costs) is made. To estimate the costs the 'Trimbos/iMTA questionnaire for costs associated with psychiatric illness' (TiC-P) is used [87,88] Quality of life is assessed by the 'EuroQol' (EQ-5D) [89] and the 'Medical Outcomes Study Short Form Health Survey – 36' (SF-36) [90]. These are validated tools for measuring general health-related quality of life.

The EQ-5D descriptive system consists of five dimensions (mobility, self-care, usual activities, pain/discomfort, and anxiety/depression), each with three levels (no problems, some problems, and extreme problems), thus defining 243 (3^5^) distinct health states.

A recent study in the Netherlands measured and valuated the EQ-5D, resulting in the 'Dutch EQ-5D tariff', which is used to calculate utilities for EQ-5D health states for the cost-utility analyses of Dutch health care programmes and treatments [91,92]

The SF-36 is a self-administered questionnaire, designed for use in clinical practice and research, health policy evaluations and general population surveys [90]. It assesses eight health concepts: 1) limitations in physical activities due to health problems, 2) limitations in social activities due to physical or emotional problems, 3) limitations in usual role activities due to physical health problems, 4) bodily pain, 5) general mental health (psychological distress and well-being), 6) limitations in usual role activities due to emotional problems, 7) vitality (energy and fatigue), and 8) general health perceptions.

The cost-utility will be evaluated by relating the difference in direct medical costs per patient, receiving either collaborative care or CAU, to the difference in terms of 'Quality Adjusted Life Years' (QALY) gained, which yields a cost per QALY estimate. Furthermore, we will also estimate the cost per QALY, including the productivity costs.

#### 3. Key effect modifier

*Physical illness *is considered to be the key effect modifier, and will be measured according to the CBS list, a questionnaire developed by the Central Bureau for Statistics (CBS) in the Netherlands. The CBS list contains 28 chronic conditions, ranging from DM type II to multiple sclerosis.

#### 4. Additional outcome measures and effect modifiers

*Depressive symptoms *will also be assessed with the 'Inventory for Depressive Symptomatology-Self Report' (IDS-SR) [81]. Remission (i.e. reduction in DSM-IV criteria below the threshold for a diagnosis of depressive disorder [68]) of depressive symptoms will be measured according to the PHQ-9. Remission on the PHQ-9 is defined as a score of five or below [86].

*Somatoform presentation *will be assessed with five questionnaires. Firstly, presentation will be assessed as the number and intensity of functional somatic complaints a patient reports on the 'Bodily Complaints Questionnaire' ('Lichamelijke Klachten Vragenlijst' [LKV]) [93]. Secondly, possible comorbid somatoform disorder will be assessed with the 'Screening for Somatoform Symptoms – 7' (SOMS-7) [94]. Thirdly, hypochondria will be measured with the 'Whitley Index' (WI) [95,96]. Fourthly, health anxiety and illness behaviour will be measured with the 'Illness Attitude Scale' (IAS) [95]. Finally, pain will be measured with one scale of the SF-36 and a visual analogue scale (VAS).

*Associated symptoms of comorbid chronic illness *will be measured as fatigue, according to the Dutch version of the 'Multidimensional Fatigue Inventory' ('Multidimensionele Vermoeidheids Index' [MVI-20]) [97,98] and as disability with the 'World Health Organization-Disability Assessment Survey-II' (WHO-DAS-II) [99].

*Preference and adherence*. Preferences of the patient will be assessed according to the choices patients make in the intervention group. Patient and provider adherence will be assessed by means of a qualitative questionnaire [57]. The working relationship between the patient and the care manager will be measured with the 'Helping Alliance Questionnaire' (HAQ-II) [100], because the care manager will provide PST [101]. The attitude of the care manager towards the treatment of depressive disorder will be measured with the Depression Attitude Questionnaire (DAQ) [102,103]

*Life-events and social support *will be assessed according to the 'Social Readjustment Rating Scale' [104] to indicate the amount of change in daily life, and by two items on the SF-36 [90].

*Personality traits *will be measured according to the neuroticism and extraversion scales of the 'NEO Five-Factor Inventory' (NEO-FFI), the abbreviated version of the NEO personality inventory [105].

*Treatment in the CAU group *will be assessed with the 'Scale assessing contacts between patients and practitioners' ('Contacten met doctors en andere behandelaars') and the 'Scale assessing medical utilization of health services' ('Vragenlijst medische consumptie') [57]. Both questionnaires measure the consumption of (medical) care of the patient.

### Power calculations

In this study, the PHQ-9 will be used as the primary outcome measure. In order to detect a standardised difference of 0.5 standard deviation in the primary outcome measure (which can be considered as a clinically relevant difference), 2 × 63 patients are needed when two-sided testing and 80% power is assumed. Intention-to-treat analysis will be applied. Therefore, 126 patients will be needed. An improvement of more than five points on the PHQ-9 can be considered a clinically relevant difference [86].

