**Methods/Design:**

CC: DIM (Collaborative Care: Depression Initiative in the Medical setting) is a two-armed randomised controlled trial with randomisation at patient level. The aim of the trial is to evaluate the treatment of depressive disorder in general hospitals in the Netherlands based on a collaborative care framework, including contracting, 'Problem Solving Treatment', antidepressant algorithm, and manual-guided self-help. 126 outpatients with diabetes mellitus, chronic obstructive pulmonary disease, or cardiovascular diseases will be randomised to either the intervention group or the control group. Patients will be included if they have been diagnosed with moderate to severe depression, based on the DSM-IV criteria in a two-step screening method. The intervention group will receive treatment based on the collaborative care approach; the control group will receive 'care as usual'. Baseline and follow-up measurements (after 3, 6, 9, and 12 months) will be performed by means of questionnaires. The primary outcome measure is severity of depressive symptoms, as measured with the PHQ-9. The secondary outcome measure is the cost-effectiveness of these treatments according to the TiC-P, the EuroQol and the SF-36.

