#### a. Effectiveness

Continuous outcome measures will be used to measure the effectiveness of the present intervention. A t-test with intention-to-treat analysis will be performed. When missing data arises, methods like 'last observation carried forward' (LOCF) or 'multiple imputation' will be used. The central effect modifier with regard to the effect of collaborative care is comorbid chronic illness. Furthermore, somatoform presentation, associated symptoms of comorbid chronic illness, preference and adherence, life-events and social support, and personality traits will be included in the analysis as potential effect modifiers. The effect size will be estimated by Chi-square analysis and described in Cohen's d. Possible confounders, such as age, gender, immigrant status, level of education, and treatment history, will be included as variables in logistical regression analysis.

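### The 126 to be randomised equals the number that must be analysed for 80% power, so any unreturned PHQ-9 at the primary visit lowers that power; intention-to-treat does not make up the difference

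*Protocol article*

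**What the plan says.** Power calculations sets the target: "In order to detect a standardised difference of 0.5 standard deviation in the primary outcome measure". It gives the requirement as "2 × 63 patients are needed when two-sided testing and 80% power is assumed". The next two sentences are "Intention-to-treat analysis will be applied. Therefore, 126 patients will be needed".

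The abstract (Methods/Design) uses the same total for randomisation: "126 outpatients with diabetes mellitus, chronic obstructive pulmonary disease, or cardiovascular diseases will be randomised". Allocation is equal: "Half of the included patients function as a control group" (Treatment of the patients in the control group). No expected loss and no inflation factor appears anywhere.

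Other sections allow for incomplete outcomes. Under Data collection, "the patients will receive assessment questionnaires by mail at baseline" and again at 3, 6, 9 and 12 months. Ethical principles lets patients withdraw consent at any time. Analyses, a. Effectiveness, specifies an intention-to-treat t-test and has a rule for gaps that begins "When missing data arises, methods like" and goes on to name last observation carried forward (LOCF) and multiple imputation.

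**The concern.** A two-sample formula counts patients whose outcome is observed. Here its result is used unchanged as the number to randomise, and the sentence order suggests that intention-to-treat is what permits this. That inference does not follow. Intention-to-treat keeps patients who stop the intervention but still return questionnaires. It cannot produce a PHQ-9 score for a patient who returns nothing.

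What is at stake is how the result is read. If some outcomes are missing, the trial does not have the stated power, and a null finding would be credited with more evidential weight against collaborative care than the design supports. The missing allowance does not by itself bias the estimate or raise the type I error.

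**Working it through.** **Inputs.** Standardised difference 0.5, two-sided test, 80% power, 63 per arm (Power calculations); 126 randomised (abstract); t-test (Analyses, a. Effectiveness). The significance level is not stated; 0.05 is assumed because it reproduces the stated number. No loss rate is stated, so 10%, 20% and 30% are assumed.

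**Reproducing the plan's figure.** n per arm = 2(z₀.₉₇₅ + z₀.₈₀)² / d² = 2(1.960 + 0.842)² / 0.25 = 62.8, so 63 per arm and 2 × 63 = 126. A one-sided test would need 50 per arm, so two-sided 5% is the setting that matches. The sample size is correctly computed for 63 analysed per arm; power there is 80.1% (normal approximation) or 79.5% (t-test).

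**Power if lost patients drop out of the t-test.** Analysed per arm m = 63(1 − loss). Normal-approximation power = Φ(0.5·√(m/2) − 1.960). At 20% loss, m = 50.4, 0.5·√25.2 = 2.510, and Φ(0.550) = 70.9%. The t-test values are slightly lower:

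| Loss | m per arm | Power for 0.5 SD (normal / t-test) | Detectable at 80% (t-test) |
|---|---|---|---|
| 0% | 63 | 80.1% / 79.5% | 0.50 SD |
| 10% | 56.7 | 75.9% / 75.2% | 0.53 SD |
| 20% | 50.4 | 70.9% / 70.0% | 0.56 SD |
| 30% | 44.1 | 65.1% / 64.1% | 0.60 SD |

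**Power if LOCF keeps all 63 per arm.** Take the unfavourable case: every lost patient in either arm has only a baseline score to carry forward, and the SD is unchanged. The expected difference then shrinks to 0.5(1 − loss):

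- 10% loss: 0.45 SD, power 70.7%
- 20% loss: 0.40 SD, power 60.6%
- 30% loss: 0.35 SD, power 49.6%

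**What baseline adjustment would have to deliver.** Adjusting for baseline PHQ-9 multiplies the residual SD by √(1 − r²), where r is the baseline–outcome correlation. To bring the detectable difference at 20% loss from 0.564 back to 0.5 SD requires √(1 − r²) = 0.5 / 0.564 = 0.887, so r² = 0.214 and r is about 0.46.

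**The case against.** The strongest reply is that the planned analysis is not a complete-case t-test. With LOCF or multiple imputation all 126 stay in the analysis, and the PHQ-9 is collected at four follow-up visits, so an imputation model may have correlated earlier scores to draw on. This stands in part. The complete-case figures illustrate the loss and are not the power of the planned analysis. But keeping 126 rows is not keeping the information of 126 observed outcomes. The protocol leaves the method open, the power statement relies on no recovery from imputation, and LOCF from baseline can be worse than complete-case. If the primary visit is 3 months, the only earlier mailed score is baseline.

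A second reply is that the last sentence may merely add up 2 × 63. That is possible. A reader might infer that the protocol declares intention-to-treat to be the reason no further patients are needed. It never says so; this is the natural reading of the sentence order combined with the absence of any allowance, and no more than that. On either reading 126 contains no allowance.

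A reader might also take the relevant loss to be that accumulated over 12 months of postal follow-up. The document does not support this, because no visit is named for the primary test. If it is the 3-month visit, loss may be smaller.

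Nor is this an arithmetic error: 63 per arm is right by the normal approximation, and the 0.6-point gap to the t-test is negligible.

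Finally, the point does not fall away because an article condenses a fuller protocol. The article itself states the calculation, the randomised total and the reasoning.

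**Conclusion.** The point holds. The number randomised equals the number that must be observed, so the stated 80% is reached only with complete PHQ-9 data at the primary visit, in a trial that itself provides for mailed follow-up, withdrawal and missing data. Intention-to-treat does not close that gap.

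The direction is clear on a t-test of the observed outcomes; the size is not known from the document. It depends on an assumed 5% level, assumed loss rates, an unnamed primary visit and an unsettled missing-data method. At 10–30% loss, power for 0.5 SD is roughly 75% to 64% on observed outcomes and roughly 71% to 50% if baseline is carried forward in both arms; well-informed multiple imputation could do better than the complete-case figures. These are moderate departures at plausible loss, with no implied bias, so this is a sample-size and power point that should be fixed, not one that invalidates the design.

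**What to change.** In Power calculations, name the visit that carries the primary test, state the significance level and the expected loss at that visit, and report the power or detectable difference that 126 randomised patients then give. Example wording at an assumed 20% loss: about 70% power for 0.5 SD, or 80% power for about 0.56 SD, on a t-test of observed outcomes. Remove intention-to-treat as the basis for the number; it belongs in the analysis section only.

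Consider adjusting the primary comparison for baseline PHQ-9, which is already collected. The gain should not be assumed. A correlation of about 0.46 would be needed to offset 20% loss, and the entry cut-off of 15 narrows the baseline range and may lower it.

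The cost is one rewritten paragraph and a less favourable power statement; no extra patients are required.

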### Analyses

A collaborative care model for the treatment of major depressive disorder in outpatients of a general hospital setting with DM, CVD, and COPD is more effective and more cost-effective than CAU, is the hypothesis underlying the present study. The primary outcome is the effectiveness in terms of the severity of the depressive symptoms, as measured by the PHQ-9. The secondary outcome is the cost-effectiveness, as measured with the TiC-P, the EQ-5D, and the SF-36.

